#### Patient-level data

The intervention occurs at the clinic level, and medical record and vaccine registry data for the cancer survivor population will be accessed by the site CRA under a HIPAA waiver as part of each site’s QI initiative. The site CRA will abstract the following data elements from the medical record for each survivor added to the study roster: Diagnosis category (leukemia, lymphoma, solid tumor, central nervous system [CNS] tumor); age at diagnosis, time from diagnosis, and time off-therapy at cohort entry; history of hematopoietic cell transplant (yes/no; if yes: type, number, age); history of Chimeric Antigen Receptor (CAR)-T cell therapy (yes/no: If yes: number, age); sex; and race/ethnicity. The CRA will abstract the following additional visit-specific data elements from the survivor’s medical record for the initial clinic visit and for each subsequent clinic visit occurring during the study period: Age at visit, study year and week of visit, provider type (physician, advanced practice provider), study identification number of healthcare provider(s) providing care at clinic visit, visit type (in-person, telehealth), and insurance type.

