### Analytic plan

#### Effectiveness trial

Unless otherwise noted, all statistical tests will be two-sided. The main hypothesis of the intervention’s effect will be tested using a mixed effects logistic regression model including a random intercept for each site. The base model for HPV vaccine initiation for participant *i* at site* j* during year* y* without covariates will be:$$\mathrm{log}\left({Odds}_{initiation,i,j,y}\right)={\beta }_{0}+{\beta }_{1}\bullet {year}_{j,y}+{\beta }_{2}\bullet {x}_{intervention,j,y}+{b}_{j}$$

where $${year}_{i,j}$$ indicates the study-year of the visit, and $${x}_{intervention,j,y}$$ equals 0 if site *j* has not been exposed to the intervention by $${year}_{j,y}$$, and equals 1 if it has, and $${b}_{j}$$ is the random intercept for site *j*. The primary hypothesis will be tested by the significance of the coefficient $${\beta }_{2}$$ in the model, which will capture the initial year of active intervention. Exploratory aims include testing whether the intervention results in increased rates of series completion and whether there is a sustained intervention effect in increasing HPV vaccine initiation. The analysis for series completion will parallel the analysis for initiation, with the exception that the analytic cohort for each year will be limited to those who had not completed the series prior to their index clinic visit for that year. Sustained effects will be tested using a similar model augmented by specific coefficients for duration of time in the intervention arm:$$\mathrm{log}\left({Odds}_{initiation,i,j,y}\right)={\beta }_{0}+{\beta }_{1}\bullet {year}_{j,y}+{\beta }_{2}\bullet {x}_{intevention,j,y}+{\beta }_{3}\bullet {x}_{2int,j,y}+{\beta }_{4}\bullet {x}_{3int,j,y}+{b}_{j}$$

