In this model, $${\beta }_{1}$$ will continue to account for a constant secular trend, while $${\beta }_{3}$$ will allow for an additional effect in the 2^nd^ year of intervention and $${\beta }_{4}$$ will similarly allow for an additional incremental effect in the third year. Thus, the log odds of initiation for a participant at site *j* in year 4 for a site in the third year of intervention will be estimated as $${\beta }_{0}+{\beta }_{1}\bullet 4+{\beta }_{2}+{\beta }_{3}+{\beta }_{4}$$ + $${b}_{j}$$. While hypothesis testing will be included in the exploratory aims, the focus will be on reporting estimated rates of outcomes and intervention effects with confidence intervals. For each outcome, secondary analyses will include patient age at visit, sex, insurance type, and race/ethnicity as covariates to improve the precision of estimates and provide an estimated standardized prevalence. We will also evaluate the impact of clinic level factors on vaccination initiation rates (e.g., clinic volume, provider characteristics, practice size, geographic location, and baseline initiation rates) as fixed effects. We will also report the HPV vaccine initiation rate among survivors who were vaccine-naïve at cohort entry (i.e., incidence of vaccine initiation). Last, we will perform subgroup analyses stratified by relevant biological variables (i.e., age at visit, sex, and race/ethnicity groups). For survivors who complete > 1 clinic visit/study year, the number and timing of subsequent clinic visits during the study period will be included as covariates in secondary analyses. Patients who develop a relapse or subsequent malignancy requiring active cancer treatment at any time during the study period will be removed from the data set as of the date of diagnosis of the relapse or subsequent malignancy. Parallel analyses will further consider providers as random effects within sites, adding a random intercept for each provider. Given the potential complexity of correlation structures and nesting, the main hypothesis tests will also be reported using permutation testing. As an example, for permutation testing the main effect based on coefficient $${\beta }_{2}$$, for multiple (> 1000) iterations, participants will be randomly assigned to sites and the models fit to develop an empirical distribution for estimates of $${\beta }_{2}$$ under the null hypothesis of not different. The p-value of $${\beta }_{2}$$ (with genuine assignments) will be estimated from distribution of coefficients estimated from the permutations.

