
*Sample Size and Power.* Based on a combination of our prior work [6], secular trends since publishing that work, and general population data regarding state-specific vaccination rates [53], pre-intervention prevalence rates of vaccine-initiated patients at the 6 sites are estimated to be 0.404, 0.496, 0.462, 0.473, 0.415, and 0.488, for an average prevalence rate of 0.456, with a stable baseline incidence initiation of 0.025 (or 2.5 absolute percentage points) [6, 53]. For evaluating the intervention, we expect to have approximately 1273 patients with clinic visits per year with site-specific numbers estimated as 227, 215, 135, 104, 403, and 189. Power was estimated using simulations making conservative assumptions about the number of available appointments, and rates of increase. From simulations, we have > 80% power to detect increased rates of initiation resulting in average prevalence after year 2 (1^st^ year of intervention) of 48.2% for the control practices vs. 57.0% for the intervention practices, an absolute difference of 8.7%, which is less than the 10% difference we expect to observe. In terms of the logistic regression model, this equates to a 6% relative increase per year in rates of incident initiation (for a secular trend with an absolute increase of 2.5%) in the control group and a 24.3% relative increase in the intervention group. Subgroup analyses: For a subgroup of half our sample (e.g., stratifying by sex, age at visit, or race/ethnicity) we have 80% power to detect a difference in rates of 49% vs. 61%.

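### Age at visit is left out of the primary model although it is collected, likely prognostic and already a planned secondary covariate; including it is a near-free improvement

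*Protocol article*

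**What the plan says.** All of this is in the protocol article; no separate analysis plan is shown.

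- **Primary model** (Analytic plan, Effectiveness trial). The base model for initiation "without covariates will be" a mixed logistic regression with an intercept, a linear study-year term, an intervention indicator and a random site intercept. "The primary hypothesis will be tested by the significance of the coefficient" beta2, the intervention term.
- **Covariates** (same section). For each outcome, "secondary analyses will include patient age at visit, sex, insurance type, and race/ethnicity as covariates to improve the precision of estimates" and to give a standardised prevalence. No reason is given for keeping age out of the primary model.
- **Data** (Patient-level data). The visit-level items abstracted begin with "Age at visit, study year and week of visit", so age is available for every observation.
- **Outcome and population** (Randomization; Inclusion and exclusion criteria). The outcome is having had at least one HPV dose by the last day of the study year, among survivors aged 9 to 17 who are at least one year off therapy. Six sites are randomised, three to each start year.
- **Power** (Sample Size and Power). The article claims more than "80% power to detect increased rates of initiation" giving "48.2% for the control practices vs. 57.0% for the intervention practices, an absolute difference of 8.7" points after Year 2, with about 1273 patients a year. Covariates are not mentioned there.

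**The concern.** An ever-vaccinated outcome can only rise with age within a person, and the population covers nine years of age around the usual time of vaccination. Age is therefore likely to be a strong predictor, yet the test that decides the trial ignores it.

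Two things are at stake. The first is power: in a logistic model, a prognostic covariate that is left out pulls the intervention log-odds ratio towards zero. The second is protection. The cohort is open, with survivors entering at 9 or at one year off therapy and leaving at 18. The site intercept absorbs stable age differences between sites, and the year term absorbs a common linear trend. Neither absorbs a change in age mix that differs by site and year, and with six sites randomised three against three, such a change need not balance out.

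**Working it through.** **Inputs from the article.** Patients per site per year: 227, 215, 135, 104, 403, 189 (sum 1273). Baseline prevalence by site: 0.404, 0.496, 0.462, 0.473, 0.415, 0.488 (mean 0.456). Effect: 48.2% against 57.0%. On sidedness: "Unless otherwise noted, all statistical tests will be two-sided". The alpha level is not stated; 0.05 is assumed.

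**Assumptions, not in the article.** Log-odds slope per year of age: 0, 0.15, 0.30 or 0.45. The corresponding prevalences at ages 9 and 17 are 46% and 46%, 31% and 60%, 20% and 73%, and 12% and 83%. Patients are treated as independent across years, and site fixed effects stand in for the random intercept.

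**1. The plan's own figure.** A two-proportion test with 1273/2 = 636.5 per arm gives 88.3% power, or 84.5% to 88.3% over the 20 possible three-against-three allocations of the sites. This meets the claimed >80%. The unadjusted base model gives 85-90% on Years 1-4, 71-77% on Years 1-3 and about 58-62% on Years 1-2. The article does not say which years or correlation its simulation used, so no error follows from this.

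**2. Effect on the model's scale.** ln(0.570/0.430) - ln(0.482/0.518) = 0.282 + 0.072 = 0.354, an odds ratio of 1.42.

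**3. Power without and with age and sex.** Years 1-3, 400 runs per row, sex log-odds ratio 0.2, Monte Carlo SE about 2 points:

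| Age slope | beta2 (SE), unadjusted | beta2 (SE), adjusted | Mean z | Power |
|---|---|---|---|---|
| 0 | 0.358 (0.139) | 0.359 (0.139) | 2.58 to 2.58 | 72% to 72% |
| 0.15 | 0.354 (0.139) | 0.368 (0.141) | 2.55 to 2.60 | 71% to 73% |
| 0.30 | 0.365 (0.139) | 0.415 (0.149) | 2.63 to 2.79 | 77% to 80% |
| 0.45 | 0.354 (0.139) | 0.471 (0.159) | 2.55 to 2.95 | 74% to 84% |

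The SE rises with adjustment, but the coefficient rises more. The ratio of squared z gives the gain in effective sample: (2.60/2.55)² = 1.04, (2.79/2.63)² = 1.13 and (2.95/2.55)² = 1.34 for slopes 0.15, 0.30 and 0.45.

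A repeat simulation comparing the model without and with age gave 76% to 76%, 71% to 74%, 76% to 80% and 72% to 85%. The gain is thus nil at slope 0 and about 10 to 13 points at slope 0.45. On Years 1-4 the first simulation gave 90% to 90%, 88% to 89%, 89% to 92% and 85% to 94%.

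**4. Type I error with chance variation in ages only.** The unadjusted test rejects a true null in 4.8%, 5.3% and 3.8% of runs at slopes 0.15, 0.30 and 0.45 (Monte Carlo SE about 1 point). There is no inflation.

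**5. Type I error under an imposed drift (stress case).** With mean age 0.5 year higher in exposed site-years and no true effect, the unadjusted beta2 averages 0.085, 0.134 and 0.184. Divided by 0.354, that is 24%, 38% and 52% of the design effect. Rejection is 7%, 17% and 26%. With random site-year shifts of SD 0.5 year, rejection is 10%, 17% and 23% (6%, 13% and 24% in the repeat simulation). The adjusted test stays at about 3-6% throughout.

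**6. How large 0.5 year is.** With ages uniform on 9 to 17 (assumed), the SD of age is √((9² - 1)/12) = 2.58 years. The chance SD of mean age per site-year runs from 2.58/√403 = 0.13 to 2.58/√104 = 0.25. For the contrast behind beta2, the SE of 0.138 on the log-odds scale with p(1-p) near 0.25 corresponds to 0.138 × 0.5 × 2.58 = 0.18 year. A shift of 0.5 year is 0.5/0.18 = 2.8 of these SDs, so it needs a real differential drift.

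**The case against.** An unadjusted primary test with prespecified adjusted secondary analyses is a recognised choice. Saying that covariates help precision does not oblige the primary model to carry them, so this is not a contradiction. The adjusted analysis, standardised prevalence, subgroups by age and initiation among vaccine-naïve survivors are all planned, and a shift in age mix would show there. All of that stands. What it leaves open is that a secondary analysis can reveal a shift but cannot protect the primary p-value; if the two disagreed, the less protected one would decide the trial.

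Three stronger readings are tempting, and the documents do not support them.

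- A reader might infer that adjustment shrinks the SE. If, for example, age explained 18% of outcome variance, linear-model arithmetic would give √(1 - 0.18) = 0.905, an SE about 10% smaller, and 1/(1 - 0.18) = 1.22, worth 22% more survivors. The planned model is logistic, where the SE of beta2 rises. An 18% share also presumes a steep age curve that the article does not give.
- A reader might infer that chance differences in age between small sites bias the test. Chance sampling of ages is already in the model's SE, and type I error stays near 5%.
- A reader might treat a 0.5-year shift as a forecast. Nothing in the article indicates a drift that differs by site and year, and survivors seen in several years would tend to keep a site's age mix stable.

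The objection that sex adds little is also right; the benefit comes from age.

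**Conclusion.** The point holds as an inexpensive improvement, not as an error in the plan. Leaving age out of the primary model costs between nothing and about 10 to 13 percentage points of Years 1-3 power over assumed slopes of 0 to 0.45 log-odds per year, through a smaller log-odds ratio. At the middle slopes of 0.15 and 0.30 the cost is about 2 to 4 points. If age were unrelated to the outcome, including it would cost essentially nothing. Age in the model also holds type I error near its nominal level if age mix drifts differently across site-years, a possibility that the article neither shows nor excludes.

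The size rests on an age gradient that must be assumed, on Years 1-3 data, on a two-sided 5% level and on independence of patients across years. The direction rests only on age predicting whether a survivor has ever been vaccinated.

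**What to change.** Prespecify age at visit, as categories or a spline, as a fixed effect in the primary model and test beta2 there. Sex may be added but is optional. Report the standardised prevalences already planned, add the risk difference between them, and keep the unadjusted base model as a sensitivity analysis.

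The cost is a change of wording in the analysis plan, made before outcome data are analysed; no new data are needed. The small downside is that the adjusted odds ratio is conditional on age and differs from the unadjusted one (at slope 0.30, a log-odds ratio of 0.415 against 0.365). The standardised rates and risk difference give readers a marginal result that avoids this difficulty.

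### Stratified subgroup analyses, powered only within one stratum, do not test whether the intervention effect differs by age, sex or race/ethnicity; an interaction estimate should be added

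*Protocol article*

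**What the plan says.** In the protocol article, Analytic plan, Effectiveness trial, the last of the additional analyses reads: "we will perform subgroup analyses stratified by relevant biological variables". The variables named are age at visit, sex and race/ethnicity. Elsewhere in that section, age, sex and race/ethnicity appear only as covariates in secondary models, as main effects. The document does not mention a term for intervention by subgroup.

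The Sample Size and Power paragraph supports the subgroup work with one sentence. It opens "For a subgroup of half our sample (e.g., stratifying by sex, age at visit, or race/ethnicity" and continues "we have 80% power to detect a difference in rates of 49% vs. 61" (per cent). This follows the overall statement that "we have > 80% power to detect increased rates of initiation", where the detectable contrast is "48.2% for the control practices vs. 57.0% for the intervention practices, an absolute difference of 8.7" points. The protocol describes that overall difference as one "which is less than the 10% difference we expect to observe".

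The section makes all tests two-sided unless otherwise noted. It gives no alpha level.

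**The concern.** A model fitted within one stratum asks whether there is an effect in that group. It does not ask whether the effect differs from that in another group. If results are presented stratum by stratum, and each stratum has been powered for detection, the natural reading is to compare p-values: the intervention works in girls and not in boys, or in one racial or ethnic group and not another. Significance in one stratum and its absence in another is not evidence of a difference.

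The trial chose sites to serve varied populations and aims at wider dissemination. A spurious statement that the intervention works in only some groups could misdirect that effort. A genuine difference could also go unquantified, because two separate confidence intervals do not give an interval for the difference between them.

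**Working it through.** **Inputs from the Sample Size and Power paragraph**
- Within half the sample: 80% power for 49% against 61%, which is 12 points.
- Overall: more than 80% power for 48.2% against 57.0%, stated as 8.7 points (the rounded rates differ by 8.8).
- Expected effect: 10 points.
- Size: "we expect to have approximately 1273 patients with clinic visits per year", so about 636 in half the sample.

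**Assumptions**
- Two-sided alpha of 0.05, so the multiplier for 80% power is 1.96 + 0.84 = 2.80.
- Normal approximation on the risk-difference scale.
- Two equal strata with independent estimates.

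**Step 1: reproduce the within-stratum figure.** Take overall power as exactly 80% at 8.7 points.
- Full-sample SE = 8.7 / 2.80 = 3.11 points.
- Half-sample SE = 3.11 × √2 = 4.39 points.
- Power for 12 points = Φ(12/4.39 − 1.96) = 78%.

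A plain two-proportion calculation for Year 2, ignoring clustering and trend, gives 82% to 86% across the 20 possible three-versus-three site allocations. The stated 80% lies between these. It came from a simulation whose full settings are not given, so it cannot be matched exactly, but it is credible as power within one stratum.

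**Step 2: chance that exactly one half is significant when the effect is the same in both.** The stated figure implies a half-sample SE of 12 / 2.80 = 4.28 points. With p = Φ(effect/4.28 − 1.96), the chance is 2p(1 − p).

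| Uniform effect | Power per half | Exactly one half significant |
|---|---|---|
| 8.7 points | 53% | 2 × 0.53 × 0.47 = 50% |
| 10 points | 65% | 2 × 0.65 × 0.35 = 46% |
| 12 points | 80% | 2 × 0.80 × 0.20 = 32% |

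**Step 3: sensitivity at 8.7 points.**
- Alpha anywhere from 0.01 to 0.10: 49% to 50%.
- Overall power of 85% or 90% instead of 80%: 49% or 47%.
- Unequal strata, from exactly 80% overall power: 55% for a 30/70 split and 61% for 20/80.
- Strata correlated through shared site-by-year shocks, with an assumed correlation of 0.25 or 0.5: about 42% or 33%.

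**Step 4: the direct comparison.** The SE of a difference between two independent halves is 4.28 × √2 = 6.06 points.
- Detectable difference at 80% power = 2.80 × 6.06 = 17 points.
- Power to detect a 12-point difference between strata = Φ(12/6.06 − 1.96) = 51%.
- With correlation ρ, the detectable difference is 12 × √(2(1 − ρ)): 14.7 points at 0.25 and 12.0 at 0.5.
- If the effect is uniform, the interaction test rejects at its nominal 5%.

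**The case against.** The strongest reply is that the protocol states no error. It plans stratified analyses, which is a legitimate way to estimate effects within groups. It gives no hypothesis of effect modification and no rule for comparing strata. A reader might infer that subgroups will be judged by which stratum reaches significance; the text does not say so, and that inference should not be attributed to the plan.

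A reader might also take the 49% against 61% sentence as wrong, or as a claim of power to detect differing effects. It is neither. It refers to a single subgroup, and Step 1 supports it on that reading.

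The figure of about half is also near a ceiling for equal independent halves, because 2p(1 − p) cannot exceed 50% and 8.7 points happens to fall almost at that maximum. It is conditional and should not be presented as a general result. The 17-point figure likewise depends on equal, independent halves.

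Finally, an interaction test might appear in an analysis plan not shown here. That limits the point but does not remove it. The article goes beyond leaving the method open: it names stratification and justifies it with detection power inside a stratum. The protocol's emphasis on estimates and confidence intervals is attached to its exploratory aims, which are series completion and sustainability, so it helps here only indirectly.

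**Conclusion.** The point holds in a limited form. The subgroup method named, with the power basis given for it, cannot show whether the intervention effect differs between groups, and it leaves readers to compare strata informally. If they compare significance, a uniform effect would appear in exactly one of two halves about 50%, 46% or 32% of the time at 8.7, 10 or 12 points. These figures assume equal independent halves and a two-sided alpha of 0.05. Correlation between strata lowers them (about 33% to 42% at 8.7 points for the correlations tried) and unequal splits raise them. All are well above the nominal 5% of an interaction test.

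The change is worth making but is not critical. The subgroup analyses are additional ones, and the primary test of the intervention coefficient is untouched.

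**What to change.** 1. For age at visit, sex and race/ethnicity in turn, fit one model on all survivors with the subgroup main effect and an intervention-by-subgroup term. Let the year trend differ by subgroup as well, so that the model corresponds to the stratified ones.
2. Report the interaction estimate with its confidence interval as the subgroup result. Give stratum-specific effects descriptively.
3. In Sample Size and Power, state that 49% against 61% is power within one stratum and that power for a difference between strata is lower. About 17 points would be needed if the halves are equal and independent. This should be confirmed with the trial's own simulation before any number is written in.

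The cost is a few model terms, one reworded sentence and a short extension of the existing simulation. No new data are needed. The only drawback is that subgroup power will look less favourable.

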### Study design, setting, and population

A hybrid type 1 effectiveness-implementation design will be used to test the effectiveness of the HPV PROTECT healthcare provider-directed intervention in improving HPV vaccine uptake in childhood cancer survivors, and to evaluate implementation outcomes (Fig. 2)*.* This study will be conducted at six participating sites (The University of Alabama at Birmingham/Children’s of Alabama, Emory University/Children’s Healthcare of Atlanta, Baylor College of Medicine/Texas Children’s Hospital, Oregon Health & Science University/Doernbecher Children’s Hospital, Atrium Health Wake Forest Baptist, and the University of Minnesota/M Health Fairview Masonic Children’s Hospital). Each of these sites have active pediatric oncology outpatient clinics that provide ongoing care for young cancer survivors 9–17 years of age and at least 1 year off-therapy, and each clinic has existing access to their state vaccine registry via their electronic medical record (EMR) system. Sites were chosen to be representative of pediatric oncology practices of varying characteristics including varied geographic location, size, and patient populations, and were especially enriched for sites serving populations in areas of lowest HPV vaccine uptake (i.e., U.S. southern states) [49, 50]. None of these sites have a standardized (quality improvement) program in place to address HPV vaccine initiation in cancer survivors. Each site has an identified Intervention Champion, who will be responsible for all aspects of the study at their site, including overseeing data collection, engaging and training providers in the targeted pediatric oncology clinics, identifying context-specific resources, assuring availability and context-appropriateness of intervention resources, providing ongoing group peer feedback/coaching sessions to providers, overseeing interface with clinic support staff in carrying out all aspects of the intervention, and assuring intervention fidelity. Each participating site has agreed to operationalize HPV PROTECT as a quality improvement (QI) initiative; therefore, all providers caring for cancer survivors will be expected to complete the training sessions, and will be given access to all intervention components at the time of intervention implementation. Healthcare providers at the participating sites will be invited, but not required, to participate in the research aspects of the project.

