### Randomization

In this stepped-wedge cluster-randomized design, randomization will occur at the site level, with three sites randomized to begin the intervention in Year 2, and three sites randomized to begin the intervention in Year 3 (Fig. 3). There is no difference in the intervention between the two groups other than the intervention start date. The study’s stepped-wedge design incorporates a control period for all participating sites during Year 1, allowing for collection of baseline vaccination rates, thus avoiding historical comparisons. Before the beginning of Year 2, sites will be randomized according to the stepped-wedge design. The sites assigned to the control condition in Year 2 (sites A, B, C) will be assigned to the intervention in Year 3, and the Year 2 intervention sites (sites D, E, F) will be moved to the post-intervention (sustainability) condition for Year 3. All sites will be assigned to the post-intervention (sustainability) condition for Year 4. The stepped wedge design will allow comparison of the primary outcome (HPV vaccine initiation rate; i.e., proportion of survivors in targeted population who have received ≥ 1 HPV vaccine dose, as of the last day of each study year) across groups (control vs. intervention), while allowing each site to serve as its own pre-intervention control, and using the control observations in Years 1 (all sites) and 2 (sites A, B, C) to estimate secular trends. Sustainability will be assessed in the post-implementation period, i.e., in Years 3 (sites D, E, F) and 4 (all sites) (Fig. 4).

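### The illustrated permutation test shuffles survivors between sites, but the trial randomises sites to start years, so its p-value is not a valid test of no intervention effect

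*Protocol article*

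**What the plan says.** The Randomization section of the protocol article states that "randomization will occur at the site level, with three sites randomized to begin the intervention in Year 2", with the other three starting in Year 3. On the two groups it adds: "There is no difference in the intervention between the two groups other than the intervention start date". The Study design section fixes the number of clusters: "This study will be conducted at six participating sites".

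The Effectiveness trial part of the Analytic plan tests the primary hypothesis by β2 in a logistic mixed model with a random intercept per site and a linear year term. It then gives a reason for a second test, "Given the potential complexity of correlation structures and nesting", and says that "the main hypothesis tests will also be reported using permutation testing". The scheme it illustrates, for β2 and with more than 1000 iterations, is that "participants will be randomly assigned to sites and the models fit to develop an empirical distribution" of β2 under the null. No section describes permuting sites or start years.

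**The concern.** A permutation test is justified in one of two ways. Either it re-enacts the randomisation, or the shuffled units are exchangeable under the null hypothesis. Neither applies here. No survivor was randomised to a site; the only random act is which three sites start first. Nor are survivors exchangeable across sites when the intervention does nothing, because the plan expects the sites to differ at baseline.

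Shuffling survivors gives every site the same expected rate in each year. The hypothesis tested is then that sites are interchangeable, not that the intervention has no effect. The shuffle also removes the site differences and any site-by-year variation, which is the correlation given as the reason for the test. What is at stake is whether a second p-value, offered as protection for the primary result, can bear that weight.

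**Working it through.** **Inputs from Sample Size and Power.**
- Patients per year by site: 227 + 215 + 135 + 104 + 403 + 189 = 1273, as stated.
- Pre-intervention prevalence: 0.404, 0.496, 0.462, 0.473, 0.415, 0.488. The mean is 2.738/6 = 0.456, as stated. The SD is 0.038, or 0.155 on the log-odds scale.

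**The plan's own figure.** It claims more than 80% power for 48.2% versus 57.0% after Year 2. A two-sided two-proportion calculation (α = 0.05 assumed; Year 2 patients independent) gives 0.883 with equal groups, and 0.845 to 0.883 over all possible splits of the sites. This agrees with the claim. The plan states no figure for the permutation test apart from the number of iterations.

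**Number of possible allocations.** C(6,3) = 6!/(3!·3!) = 720/36 = 20.
- With more than 1000 shuffles, the participant scheme can report p near 1/1001 ≈ 0.001.
- A test based on the 20 allocations cannot go below 1/20 = 0.05.
- Using Years 1–3, the exposure indicator minus (year − 1)/2 is ±1/2 in Year 2 and 0 in the other years. Swapping the two sequences then reverses the sign of β2 exactly, every allocation ties with its mirror image, and the floor is 2/20 = 0.10.
- Using Years 1–4, exposure in Year 4 is 1 where the line would give 1.5. The tie is broken and the floor is 1/20.

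**Type I error of the participant shuffle.** These are simulations with no intervention effect, the plan's site sizes and rates, and nominal two-sided 5%. The logistic mixed model was approximated by a random-intercept model on site-by-year empirical logits.

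*Different survivors each year, shuffled within year:*

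| Site-by-year SD (log-odds, assumed) | Years 1–4 | Years 1–3 |
|---|---|---|
| identical sites, 0 (control case) | about 4–5% | about 4–5% |
| plan's site rates, 0 | 6–8% | about 10% |
| plan's site rates, 0.10 | 13–15% | 18% |
| plan's site rates, 0.15 | 19–24% | 26% |

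The control case locates the cause: with identical sites the shuffle holds its level, and with the plan's site differences it does not. In the three-year model without site-by-year variation, the shuffled β2 has SD 0.113 against a true SD of about 0.14. In the four-year model the corresponding figures are 0.085 and 0.094, the latter measured around each dataset's own permutation mean, because the shuffle holds the overall yearly totals fixed.

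*Survivors returning, each moved with all of his or her years (assumed 60% to 100% returning each year; three- and four-year models):*
- no site variation in incidence: 0.7% to 6%;
- moderate variation: 2% to 11%;
- strong variation (site-by-year SD of 1.0 in log-odds of yearly initiation, 0.2 in entrants' prevalence): 16% to 18%.

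A separate set of four-year runs gave 2.9% (SE 0.7) at 60% returning, and 4.2% (SE 1.2) at 80%. At 80% returning with a log-SD of 0.5 in site incidence it gave 4.5% (SE 0.9).

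**The case against.** The strongest reply concerns direction. A reader might infer that the permutation p-value is bound to be too small and would falsely corroborate a chance finding. The protocol does not support that. Its Patient-level data section says survivors seen in more than one year are linked, and a survivor who has initiated stays initiated. If participants are shuffled as whole persons and most return, the error rate is near nominal or conservative unless incidence varies strongly by site. The returning share, the site-by-year variance and the exact unit shuffled are not given. This part of the reply stands.

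A reader might also infer that the planned 1000 or more iterations are impossible. They are not: reassignments of participants are plentiful. The limit of 20 applies only to re-randomisations of sites.

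Nor does the point invalidate the primary analysis. The permutation result is reported in addition to the model test, and the scheme is introduced as an example. That lowers the weight of the point but does not remove it. The example is the only scheme described, it concerns the main coefficient, and it is a stated procedure rather than a detail left to an analysis plan.

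**Conclusion.** The mismatch is certain from the text: sites are randomised to start years, and the illustrated test reassigns survivors to sites. Its reference distribution does not follow the design, and its p-value is not a valid test of no intervention effect.

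The size and direction of the error are not determined by the protocol. The simulated four-year range runs from about 1% (closed or nearly closed cohort, stable sites) to 24% (independent yearly samples, site-by-year SD 0.15). All of these figures rest on assumed carry-over, assumed site-by-year variance and an assumed α of 0.05. The point should be fixed before analysis, but it affects a supplementary test only. The mixed-model estimate, interval and p-value for β2 do not change because of it.

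**What to change.** Replace the illustrated scheme with text along these lines: the model is refitted under each of the 20 possible allocations of the six sites to the two start years, with every survivor and all of his or her years kept in the original site; the p-value is the share of allocations, the actual one included, whose |β2| is at least as large as that observed.

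State the floor alongside it: 1/20, or 2/20 where the statistic is symmetric in the two sequences, according to the years and model fitted. Say that the test is supportive only, cannot give p < 0.05, and leaves the mixed-model test of β2 as the primary test.

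The cost is one paragraph and 20 model fits instead of more than 1000. The price is resolution. At the plan's 48.2% versus 57.0%, the site permutation reached p ≤ 0.05 in about 60% of simulated four-year trials, and never with Years 1–3, where the floor is 0.10. Its type I error at p ≤ 0.05 in the four-year model was 5.2% to 5.5%. That limit comes from having six clusters and should be stated before the results are known.
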